#### Baseline visit

The baseline visit will take place in the patient’s GP practice. The researcher will assess the patient’s eligibility and obtain written informed consent (Additional file 5). The researcher will check for eligibility based on the patient’s medical history, medication use, current e-cigarette use and smoking status, which will be biochemically verified through exhaled carbon monoxide (CO) readings. Medical history and medication use may be checked against the participant’s primary care records to ensure accuracy and completeness. The researcher will also collect basic demographic data, information on smoking history and a saliva sample. Table 1 outlines the data that will be collected at baseline.

**Table 1 Tab1:** Data collection at baseline visit

Demographics	Basic demographic information
Medical history	Medical problems and concomitant medication
Smoking history	Information on smoking and quitting history (age when started smoking, number of cigarettes smoked per day, when the last cigarette was smoked, type of cigarettes smoked per day (roll-ups or factory-made), usual pack/pouch size, nicotine dependence, motivation to stop smoking, self-efficacy and outcome expectancies, history of any pharmacotherapy or e-cigarette use and exhaled CO measurement)
Biological samples	Saliva samples to measure anabasine (for smoke intake) and cotinine (for nicotine intake)

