#### Secondary outcomes

Secondary outcome measures for abstinence include 7-day point prevalence abstinence measured at 8 months, biochemically confirmed by an exhaled CO of < 10 ppm. We will also measure 6-month prolonged abstinence using the Russell standard criteria, defined as smoking fewer than five cigarettes between 2- and 8-month follow-ups, confirmed by an anabasine concentration of < 1 ng/ml at 2 months and an exhaled CO concentration of < 10 ppm at 8 months (or anabasine concentration of < 1 ng/ml at 8 months if CO measurement unavailable). There is no funding for analysing all saliva samples at 8 months; therefore, we will verify abstinence using exhaled CO in the first instance.

As an additional measure of smoking reduction, we will assess the mean change in salivary anabasine concentrations from baseline to 2 months.

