### Analysis plan

#### Primary and secondary analyses

The proportion of participants who reduce smoking in each group will be presented. A log-binomial regression model will be applied to the data and the treatment effect will be reported as a relative risk and 95% confidence interval, adjusted for GP practice. A similar procedure will be used to analyse the proportion of participants who abstain from smoking. Analyses will be carried out on an intention-to-treat basis, according to the Russell Standard [60], where participants lost-to-follow up are assumed to be smokers or not to have reduced and we will impute missing anabasine concentrations with the baseline value.

The mean (SD) change in salivary anabasine from baseline to 2 months will be reported for each group and the difference and 95% CI will be computed using linear regression with adjustment for GP practice. Assumptions of linear regression will be assessed and if violated a Mann-Whitney test will be adopted and the median (IQR) will be used to summarise the data and difference in medians (95% CI) will be reported.

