#### Other analyses

For examining uptake and use of e-cigarettes, we will calculate the proportion of participants who take up the offer of an e-cigarette and the proportion who continue to use them at 2- and 8-month follow-ups. Proportions will be reported using descriptive statistics. Continued use of e-cigarettes will mean either use until complete smoking cessation was achieved or continued use on > 50% days between baseline and follow-up. For changes in nicotine intake, we will calculate the mean change in salivary cotinine concentrations from baseline to 2-month follow-up for each group and the difference and 95% CI will be computed using linear regression with adjustment for GP practice. Assumptions of linear regression will be assessed and if violated a Mann-Whitney test will be adopted and the median (IQR) will be used to summarise the data and difference in medians (95% CI) will be reported.

We will compare the proportion of people who consent to enrolment into the study and complete 2- and 8-month follow-ups. We will examine these outcomes separately at each recruitment centre to assess the generalisability of our recruitment procedures. Proportions will be reported using descriptive statistics and the difference between trial arms and 95% CI will be calculated.

For participants’ views of the programme (assessed by Likert scale questions), we will calculate the total score and compare these by trial arm using linear regression with adjustment for GP practice. Participants’ recall of key points of the consultation (reported as a yes/no variable) will be presented as frequencies and compared between the two arms using a chi-squared test.

Practitioner fidelity to the intervention will be assessed using a rating scale for key elements in the behavioural interventions and summarised as a score. These are descriptive process data and relate only to the intervention group.

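### The anabasine and cotinine change analyses omit the baseline concentration, and their fallback test drops practice: precision given up at no saving

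*Protocol article*

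**What the plan says.** Under Secondary outcomes, the protocol article introduces the biomarker measure: "As an additional measure of smoking reduction, we will assess the mean change in salivary anabasine concentrations from baseline to 2 months". Under Primary and secondary analyses it sets out the summary, "The mean (SD) change in salivary anabasine from baseline to 2 months will be reported for each group", and the comparison, in which "the difference and 95% CI will be computed using linear regression with adjustment for GP practice". For nicotine intake, Other analyses says that "we will calculate the mean change in salivary cotinine concentrations from baseline to 2-month follow-up for each group", with the same regression and the same adjustment.

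Both analyses have the same fallback. Regression assumptions are checked, and "if violated a Mann-Whitney test will be adopted and the median (IQR) will be used to summarise the data", with a difference in medians and its 95% CI.

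Three other parts of the article bear on this:

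- Table 1 (Baseline visit) lists saliva collection for both biomarkers. That visit comes before the annual review at which the envelope is opened.
- Randomisation and blinding makes practice the stratification factor.
- Primary and secondary analyses states that "we will impute missing anabasine concentrations with the baseline value", and Sample size expects 70% follow-up. No such rule is stated for cotinine.

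The baseline concentration is not named as a covariate anywhere in the article.

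**The concern.** A change score fixes the slope of the 2-month value on the baseline value at 1. If the true slope is below 1, patients with high baselines tend to fall more, and the change score over-corrects. Any chance difference in baseline between the arms then passes into the estimate, and the residual variance is larger than it need be. Including the baseline value lets the data set the slope.

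The fallback adds to this. A plain Mann-Whitney test uses neither practice nor the baseline value. The reported quantity also moves from a difference in means to a difference in medians, depending on how the residuals look. If the baseline-value rule carries over to the change analysis, up to about 30% of anabasine changes would be exactly zero, so a failed residual check is a realistic prospect.

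At stake is the precision of the trial's continuous biochemical measure of smoking reduction, and of the comparison that asks whether patients reduce or replace their nicotine intake.

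**Working it through.** **The plan's own figures.** The article gives no sample size, SD or correlation for either biomarker, so there is nothing to reproduce for them. Its 320 patients are sized on the two binary primary outcomes. At 160 per arm, reduction (8% v 8% × 2.8 = 22.4%) has 91.5% power at two-sided 0.025. Cessation (5% v 5% × 3.4 = 17%) has 88.7% at 0.025 and 93.3% at 0.05. These are close to the stated 90%, and the present point does not touch them.

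**Inputs.** From the documents: 160 per arm, 70% expected follow-up, missing anabasine set to baseline. Assumed: correlation r = 0.3, 0.5, 0.7 between baseline and 2 months, and equal SDs s at the two times.

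**1. Change score against baseline-adjusted regression.**

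- Variance of change: 2(1−r)s². Variance given baseline: (1−r²)s².
- Ratio: (1−r²)/[2(1−r)] = (1+r)/2.

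| r | ratio | variance saved | CI narrower, 1−√ratio |
|---|---|---|---|
| 0.3 | 0.65 | 35% | 19.4% |
| 0.5 | 0.75 | 25% | 13.4% |
| 0.7 | 0.85 | 15% | 7.8% |

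An effect with 80% power by change score would have 93.5%, 89.9% or 86.0% with baseline added.

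**2. Anabasine with baseline-value imputation.** Let a fraction p = 0.3 of follow-up values equal baseline, missing at random, with no average shift between visits. The slope becomes b = p + (1−p)r. The variance of change is 2(1−p)(1−r)s² and the variance given baseline is (1−b²)s². Since 1−b = (1−p)(1−r), the ratio is (1+b)/2.

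| r | b | ratio | variance saved | CI narrower |
|---|---|---|---|---|
| 0.3 | 0.51 | 0.755 | 24.5% | 13.1% |
| 0.5 | 0.65 | 0.825 | 17.5% | 9.2% |
| 0.7 | 0.79 | 0.895 | 10.5% | 5.4% |

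A simulation of 400,000 records per r gives ratios of 0.754, 0.827 and 0.896, in agreement.

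**3. Unequal SDs.** With k = SD at 2 months / SD at baseline, the ratio is k²(1−r²)/(1+k²−2rk). At r = 0.7 it is 0.63 for k = 0.8, 0.85 for k = 1 and 0.98 for k = 1.25. At r = 0.8 and k = 1.25 the slope rk equals 1 and the gain is nil. In large samples the ratio never exceeds 1.

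**4. Chance imbalance.** With equal SDs, a baseline difference of d between arms shifts the change-score estimate by −(1−r)d. One standard error of the baseline difference is s√(2/160) = 0.112s. An imbalance of that size shifts the estimate by 0.078s, 0.056s or 0.034s for r = 0.3, 0.5, 0.7.

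**5. Dropping practice.** The standard error grows by about 1/√(1−ICC) − 1. That is 0.5%, 1.0%, 2.6% or 5.4% for an assumed ICC of 0.01, 0.02, 0.05 or 0.10.

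**The case against.** Several points on the other side stand.

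- A reader might infer that the change score is biased. Under randomisation it is not. The issue is precision, and the shift that a particular chance imbalance causes.
- A reader might apply the 35/25/15% savings to anabasine. If its imputation rule covers the change analysis, that rule pulls the slope towards 1 and shrinks the gain to the second table. The larger figures could apply to cotinine, and then only with equal SDs.
- A reader might call the switch of test post hoc. The check and the fallback are both written in advance. The choice depends on the data, but it is pre-specified.
- A reader might fault the median interval because a Mann-Whitney test does not yield it. The article does not say that it does, and the interval method is ordinary analysis-plan detail.
- Losing practice costs little unless the ICC is large, and a rank test can be efficient for skewed concentrations.
- A log-scale model might look like the obvious remedy. It would replace the stated outcome, mean change in concentration, with a ratio. It is also sensitive to the value used below the assay limit. As an illustration, assume 17% v 5% abstinent and a geometric mean of 10 ng/ml in everyone else. Substituting 0.5, 0.1 or 0.01 ng/ml for abstainers gives ratios of (0.5/10)^0.12 = 0.70, (0.1/10)^0.12 = 0.58 or (0.01/10)^0.12 = 0.44.

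An appeal to an unseen analysis plan does not dispose of the point: the article itself names the adjustment and the fallback.

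**Conclusion.** The point holds as a free improvement. The article fixes an analysis of change adjusted for practice only, while a strong candidate covariate is already collected before randomisation. The fallback then drops the stratification factor and changes the quantity reported.

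The size is a range under assumptions, because the documents give no SDs, correlations or ICC. The equal-SD savings in the working, for r from 0.3 to 0.7, are the best single guide, with the smaller set applying to anabasine under 30% baseline-value imputation. The gain would be larger if the 2-month SD is below the baseline SD. It can vanish if the slope is 1.

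A reader might infer that the trial's main conclusions are at risk. They are not. Anabasine change is a secondary outcome and cotinine an other measure; neither enters the Holm procedure or the sample size of 320.

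**What to change.** In both linear regressions, add the baseline concentration of the same biomarker as a covariate alongside arm and GP practice. The arm coefficient still estimates the difference in mean change. It is the same whether the dependent variable is the 2-month value or the change, so the stated outcome is kept.

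If residual assumptions fail, keep this model and take robust or bootstrap confidence intervals. Report any rank test, stratified by practice (van Elteren), as a sensitivity analysis. A log-scale model is optional; if used, state beforehand the value assigned to results below the assay limit.

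The cost is a change of analysis wording and one degree of freedom per model, with no new data. The article's Trial status section places the trial in follow-up at resubmission, so the change could be recorded before the analysis.

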#### Other analyses

For examining uptake and use of e-cigarettes, we will calculate the proportion of participants who take up the offer of an e-cigarette and the proportion who continue to use them at 2- and 8-month follow-ups. Proportions will be reported using descriptive statistics. Continued use of e-cigarettes will mean either use until complete smoking cessation was achieved or continued use on > 50% days between baseline and follow-up. For changes in nicotine intake, we will calculate the mean change in salivary cotinine concentrations from baseline to 2-month follow-up for each group and the difference and 95% CI will be computed using linear regression with adjustment for GP practice. Assumptions of linear regression will be assessed and if violated a Mann-Whitney test will be adopted and the median (IQR) will be used to summarise the data and difference in medians (95% CI) will be reported.

We will compare the proportion of people who consent to enrolment into the study and complete 2- and 8-month follow-ups. We will examine these outcomes separately at each recruitment centre to assess the generalisability of our recruitment procedures. Proportions will be reported using descriptive statistics and the difference between trial arms and 95% CI will be calculated.

For participants’ views of the programme (assessed by Likert scale questions), we will calculate the total score and compare these by trial arm using linear regression with adjustment for GP practice. Participants’ recall of key points of the consultation (reported as a yes/no variable) will be presented as frequencies and compared between the two arms using a chi-squared test.

Practitioner fidelity to the intervention will be assessed using a rating scale for key elements in the behavioural interventions and summarised as a score. These are descriptive process data and relate only to the intervention group.

The patient, practitioner and vape team interview analysis will follow the Framework approach [61], categorising data into cases and coded themes. We will follow an inductive approach, drawing on participants’ perspectives and experiences of the intervention to develop a coding matrix. Interviews will be analysed as the data are collected so that insights from initial data analysis can be explored in later interviews and used to refine themes and categories. We will carry out this process until data saturation is reached, where no new themes emerge. Data will be analysed using NVivo software.

We will analyse intervention delivery during the consultations using conversation analysis (CA), a well-established qualitative methodology used to analyse the sequential organisation of verbal and non-verbal aspects of talk-in-interaction [62]. CA has been extensively applied in routine healthcare, particularly in general practice settings [63], and is now beginning to be applied to the analysis of talk-based healthcare interventions in RCTs [64, 65]. The aim is to uncover differences in the communication practices used by clinicians that seem more or less effective at persuading participants to take and try using e-cigarettes. We will transcribe and analyse a sample of 50 audio-recordings using this technique, firstly by identifying the consultations that resulted in patients trying an e-cigarette and comparing communication practices and patient uptake across practitioners. Most communication training uses instruction or role-play but this often fails to give insight into the complexity of real-life encounters. Real examples of ‘trainables’ from the CA analysis, highlighting ‘what works’, i.e. the kind of interactional issues that can occur during intervention delivery and the techniques that can best resolve them, will be collected to inform future work. By doing so we will be able to demonstrate both ‘plausible framings and efficacious implementations’ of our intervention, and ways in which communication behaviour change can be incorporated into an existing clinical skillset [66].

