## Methods/design

### Study design

This is a two-centre, individually randomised, two-arm, parallel group study. The study will take place in general practices in England. Smokers with a smoking-related chronic disease or SMI and who have no intention of stopping immediately or seeking cessation support will be randomised to one of two groups, if they decline referral to NHS stop smoking services (SSS) and smoking cessation medication: an intervention group offered encouragement by their practitioner to use an e-cigarette, or a standard care control group who will receive nothing beyond the usual care already provided prior to randomisation. Participants in the intervention group will be offered an e-cigarette starter pack and accompanying practical support booklet; this will contain details for a telephone call back service run by experienced vapers for technical support and a website with an online video tutorial. Patients will attend four visits at their GP practice: a baseline visit, a therapeutic visit with their GP or nurse and two follow-up visits 2 months and 8 months post-consultation.

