### Randomisation and blinding

Participants will be randomised to intervention or control with a 1:1 allocation ratio. A randomisation list will be generated by the trial statistician using the current version of Stata and validated by a second statistician within the Primary Care Clinical Trials Unit (PC-CTU). The randomisation will be stratified by practice and will use varying block sizes to ensure allocation concealment. The randomisation list will then be passed to someone independent of the trial who will create the randomisation envelopes.

Practitioners will randomise patients during the annual review appointment. On the day of the annual review session, a researcher will give each practitioner a set of opaque A5 sealed envelopes, which will contain a colour-coded randomisation card. The envelopes will be numbered in sequence. The GP or practice nurse will only open the randomisation envelope after they have delivered usual care advice on smoking and are satisfied that the patient meets eligibility for the trial, i.e. the patient confirms that s/he is currently a smoker and declines usual care treatment for stopping smoking. The patient is classed as enrolled in the trial only after the randomisation envelope has been opened. The randomisation card inside the sealed envelope will reveal the patient’s treatment allocation to the GP or nurse, but not the patient. The randomisation envelope will be returned to the researcher by the patient after their consultation.

If the patient is no longer a smoker or accepts usual care treatment, practitioners will fill in a patient ineligibility card containing a tick box option to select if they did not randomise and enrol the patient into the trial. The tick box will indicate the reason for non-enrolment, i.e. patient has stopped smoking, patient accepted usual care or any other reason where it is deemed clinically inappropriate. The ineligibility card will be returned to the researcher after the session and the patient will be thanked for their time given to the study and debriefed.

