#### Therapeutic visit

Participants will be invited to attend an annual review appointment for their chronic condition in the new QOF year, from April 2018. The intervention will be delivered by the GP or practice nurse during this appointment.

A researcher will be present in the GP practice on the day of the participant’s annual review appointment to remind practitioners of the study procedures and to collect data after the consultation. Neither clinicians nor patients are reliable reporters of their communication behaviour [55] and recording does not seem to change consultation content or behaviour [56]. Therefore, audio recordings will be used to monitor adherence to the intervention (including quality of delivery as well as immediate patient responsiveness) and the degree of local tailoring being adopted across practitioners and practices. The recordings will be checked by the study team using a study-specific behaviour checklist.

During the consultation, the practitioner will enquire about the participant’s smoking status. If the participant reports that they no longer smoke, the practitioner will complete a patient ineligibility card and cease to provide any further smoking cessation advice. If the participant confirms that they are a smoker, the practitioner will deliver usual care as outlined below. The GP/practice nurse will open a randomisation envelope if the participant is eligible for the trial, i.e. the participant declines usual care treatment. Participants randomised to the control group will be given no further advice beyond what they have been given (i.e. offered usual care), while the intervention group will be offered an e-cigarette starter pack and support materials. At the end of the consultation, all participants will be asked to return the randomisation card and envelope to a researcher who will be waiting in another room. The researcher will then ask the participant to complete a post-consultation questionnaire to assess the quality of advice given during their consultation and contamination, via recall of key points of the consultation. The consultation audio-recording will be reviewed if the post-consultation questionnaire reveals that contamination has occurred, i.e. participants in the control group recall that e-cigarettes were mentioned by the GP/nurse. If the recording confirms contamination, the researcher will deliver brief refresher training to the practitioners concerned.

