#### Two-month follow-up

Study staff will contact participants and schedule a follow-up appointment at the GP practice or carry out a home visit 2 months after randomisation. At this visit, the researcher will record information on the types of medication currently used, and any adverse events. S/he will collect information on smoking behaviour including self-reported smoking status, the number of cigarettes smoked per day, current pack/pouch size, use of e-cigarettes and pharmacotherapy (NRT, varenicline or bupropion) and nicotine dependence. A saliva sample and exhaled CO measurement will be taken by the researcher. S/he will also record whether the participant accessed any type of support (e.g. NHS SSS) for stopping or reducing smoking since randomisation. If the participant reports that they have stopped smoking and they are taking a particular medication that requires a dose adjustment due to this, the participant’s GP will be informed. For intervention group participants, we will assess the frequency of telephone support and use of the online video tutorial. If participants are unable to attend a practice visit or a home visit, information on smoking behaviour will be collected by telephone, text message or email. Salivettes will be posted out to participants with instructions on how to give a saliva sample and a pre-paid envelope will be provided for returning the sample back to the study team.

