### Statistics and analysis

#### Sample size

In order to correct the type 1 error rate for the fact that there are two primary outcomes we will be using the Holm-Bonferroni method of adjustment [59]. The smaller *P* value will be compared to an alpha of 0.025 (this will probably be for reduction in smoking) and if this is significant, the larger *P* value (which will probably be for cessation) will be compared to an alpha of 0.05. A total sample size of 320 will allow us to detect a risk ratio of 2.8 for the proportion of patients reducing their smoking and a risk ratio of 3.4 for the proportion of patients who stop smoking [38]. This assumes power of 90% and control group rates of 5% and 8% for stopping and reducing, respectively [38]. No allowance will be made for loss to follow up as all such cases will be assumed to have continued their baseline level of smoking.

We expect to see adherence to the behavioural intervention by practitioners of 70%, use of the e-cigarette at follow-up of 40%, and follow-up 70% of enrolled participants. We will be able to estimate these proportions with 95% confidence intervals being no greater than ±8% with a sample of 160 people in the intervention group and ±6% for the whole sample of 320 participants.

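### The 50%-of-days rule for continued e-cigarette use starts its count at the baseline visit, before the device is offered, and so under-counts continued use

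*Protocol article*

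**What the plan says.** Under Other analyses, the protocol article gives a two-part definition: "Continued use of e-cigarettes will mean either use until complete smoking cessation was achieved or continued use on > 50% days between baseline and follow-up". The denominator of the second part is thus the "days between baseline and follow-up". It reports the resulting proportion at 2 and 8 months, descriptively.

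The visit sequence is set out elsewhere in the article:

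- Study design lists "a baseline visit, a therapeutic visit with their GP or nurse and two follow-up visits 2 months and 8 months post-consultation". Baseline and therapeutic visits are distinct, and follow-up runs from the consultation.
- Baseline visit: "The researcher will assess the patient’s eligibility and obtain written informed consent". Demographics, smoking history and a saliva sample are also taken. No device is supplied.
- Randomisation and blinding: "Practitioners will randomise patients during the annual review appointment".
- Therapeutic visit, on the annual review: "The intervention will be delivered by the GP or practice nurse during this appointment".
- Two-month follow-up: staff are to "schedule a follow-up appointment at the GP practice or carry out a home visit 2 months after randomisation". The 8-month contact follows 6 months after that visit.
- Exclusion criteria: people already using e-cigarettes are not eligible.

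**The concern.** The rule measures persistence with a device, but its clock starts before anyone has the device. The days from the baseline visit to the annual review add to the denominator and, for the study device, can add nothing to the numerator. A participant therefore has to vape on more than half of the days after the offer to pass a rule that nominally asks for half.

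Uptake and use of the offered e-cigarettes is a stated secondary objective in a trial whose aim includes feasibility and acceptability. The participants at risk of losing the label are those who vape on somewhat more than half of days and go on smoking. The distortion also differs between the two time points at which the proportion is reported, because the same gap is divided by a much longer period at 8 months.

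**Working it through.** **Is there a gap?** The article does not state its length, but it presupposes one. Exclusion criteria refer to plans to stop before or at the annual review. Therapeutic visit provides an ineligibility card for a patient who no longer smokes by then.

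**Does baseline mean the baseline visit?** The sentence after the definition measures change in salivary cotinine from baseline to 2 months, and that saliva is collected at the baseline visit. Where the article means the treatment clock, it refers to randomisation or the consultation.

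**Inputs.** T is the number of days from offer to follow-up: 61 for 2 months and 243 for 8 months (calendar conversions of the stated schedule). g is the number of days from the baseline visit to the offer. It is not given, so values of 7, 14 and 30 are assumed. Study-device use during g is zero, and any other e-cigarette use in g is taken as zero because current users are excluded.

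**Plan's own figure.** The article gives no figure for this threshold or for the gap, so there is nothing to reproduce.

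**Formula.** As written, days of use must exceed 0.5 × (g + T). As a share of the days on which use was possible, that is 0.5 × (g + T)/T = 0.5 × (1 + g/T). Counted from randomisation, g = 0 and the share is 0.5.

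| Gap g (assumed) | 2 months: required share | Days needed of 61 | 8 months: required share | Days needed of 243 |
|---|---|---|---|---|
| 0 (count from randomisation) | 50% | 31 | 50% | 122 |
| 7 | 0.5 × 68/61 = 55.7% | 35 | 0.5 × 250/243 = 51.4% | 126 |
| 14 | 0.5 × 75/61 = 61.5% | 38 | 0.5 × 257/243 = 52.9% | 129 |
| 30 | 0.5 × 91/61 = 74.6% | 46 | 0.5 × 273/243 = 56.2% | 137 |

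**Who changes category.** At 2 months, participants who do not qualify by the cessation branch and used the device on 31–34 days (g = 7), 31–37 days (g = 14) or 31–45 days (g = 30) of 61. At 8 months, the bands are 122–125, 122–128 and 122–136 days of 243.

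**Limiting case.** At g = 61 the 2-month rule asks for more than 0.5 × 122 = 61 days out of 61, so even daily use after the offer would fail this branch. Nothing in the article says that gaps are this long.

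**Across time points.** Take g = 14 and steady use on about 57% of days after the offer. At 2 months that is 35 of 61 days, which fails because 38 are needed. At 8 months it is 139 of 243, which passes because 129 are needed. Counted from randomisation, it passes at both.

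**The case against.** The best defence is that the affected group is narrow and the measure minor. Anyone who vaped until they stopped smoking qualifies whatever the denominator. Near-daily users pass under either start point unless the gap is long. The measure is listed among the other and exploratory outcomes and reported without a test. At 8 months, with a gap of a week or two, the shift is 1 to 3 percentage points. All of this stands, and it limits the size of the point. It does not make the rule right.

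Baseline might also have been loose shorthand for the start of treatment. That is possible, but it would give the word two meanings in adjacent sentences.

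Three stronger readings are tempting, and the article does not support them:

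- *Real users are recorded as non-users.* Acceptance of the starter pack is reported separately, and the follow-up questionnaires also collect sessions per day and days of use. Those affected lose only the continued-use label.
- *The planning figure of 40% is undermined.* Sample size refers to "use of the e-cigarette at follow-up of 40%, and follow-up 70% of enrolled participants" without tying it to the 50%-of-days rule. It could equally mean current use at the time of follow-up.
- *Use rates cannot be compared between practices or centres.* The planned by-centre examination covers enrolment and completion of follow-up, not this measure.

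**Conclusion.** The point holds as a wording error in one descriptive measure of a secondary objective. As written, the rule can only under-count continued use, and it does so more at 2 months than at 8. For assumed gaps of 7 to 30 days, the effective threshold is about 56% to 75% at 2 months and 51% to 56% at 8 months, against an intended 50%.

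The direction follows from the visit sequence and from e-cigarette use before the offer being about zero, which is certain for the study device and expected for any other. The size depends on a gap that the article does not give. The number of participants who would change category cannot be estimated from it. The primary outcomes, the sample size and the proportion accepting a starter pack are not affected.

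**What to change.** In the definition of continued use, start the count at randomisation (the therapeutic visit) instead of baseline, and keep each follow-up as the end point. The 50% criterion and the cessation branch stay as they are.

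The cost is a small wording change in the protocol and in any analysis plan that repeats the rule. The randomisation date must already be held, because the 2-month visit is scheduled from it, and the number of days of e-cigarette use is already a questionnaire item. No new data appear to be needed. Trial status places the study in follow-up when the article was resubmitted; on that timing the change could be made before database lock.
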